### Statistical power

We expect that each of the six referral networks will enroll at least 200 participants. Given the longstanding history of the AMPATH CDM program and robust clinical infrastructure in our catchment area, as well as previous success in recruiting participants for community- and clinical-based research related to hypertension and other chronic diseases, we anticipate being able to successfully enroll our needed number of participants. To augment this, we have sensitized all participating AMPATH CDM staff on the STRENGTHS trial, and conducted training of clinicians on the AMPATH CDM hypertension treatment and referral guidelines. Through our baseline needs and contextual assessment (Aim 1), clinic staff have become well versed on the eligibility criteria and enrollment procedures, which will also help with recruitment for the trial. During our pilot testing, if we encounter difficulty with recruitment or enrollment, then we will put additional strategies in place to overcome this. We estimate a 10-mmHg reduction in SBP in the intervention arm compared to the usual care arm [68]. For our power calculation, we set the type I and type II error rates at 5% and 20%, respectively. We account for within-cluster correlation using intra-class correlation (ICC) values ranging from 0.02 to 0.06 consistent with prior studies using SBP as the outcome [69]. We analyze scenarios over a range of minimum detectable differences (MDD) assuming a standard deviation (SD) for change in SBP of 15 from the literature, with SD ranges from 10 to 20 [69, 70]. Finally, we assume that up to 15% of enrolled participants will be lost to follow-up. Table 1 presents expected power assuming a standard deviation of 15 for the comparison across different combinations of ICC and minimum detectable differences (MDD). Over a wide range of plausible ICC, with standard deviation fixed at 15, we will be able to detect a mean difference in change in SBP consistent with the published literature [69, 70] and our preliminary data [71, 72] with power greater than 80%.

**Table 1 Tab1:** Estimated power over a range of ICC and MDD values

MDD	ICC				
	0.02	0.03	0.04	0.05	0.06
4	36	27	22	19	17
6	65	51	42	36	32
8	87	74	64	56	50
10	96	89	82	74	67
12	99	97	92	87	82
14	99	99	98	95	91

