## Methods/design

### Setting

The Academic Model Providing Access to Healthcare (AMPATH) program is an academic global health partnership between Moi Teaching and Referral Hospital (MTRH), Moi University College of Health Sciences, and a consortium of North American universities led by Indiana University [33–35]. In recognition of the growing non-communicable disease (NCD) burden in LMICs [36], AMPATH has established a Chronic Disease Management (CDM) Program in collaboration with the Ministry of Health (MOH). The CDM Program has enrolled over 15,000 patients with hypertension at 69 facilities spanning all levels of the health system, alongside system-wide approaches to task redistribution, use of mHealth and electronic decision support, and ensuring a reliable supply of medicines for hypertension and other NCDs [37–39]. At MTRH, there is an inpatient cardiac critical care unit, a specialist outpatient cardiology clinic, and advanced cardiac diagnostic services [40]. It is within this clinical infrastructure that we plan to develop and test our intervention.

We will conduct this study within the AMPATH CDM program’s catchment area across eight geographically separate referral networks (Fig. 1). The Kenyan public-sector health system functionally coalesces into the three traditional health system levels—primary, secondary, and tertiary—and each referral network in our catchment area is centered around a secondary-level health facility: Kitale, Webuye, Kocholya, Turbo, Mosoriot, Burnt Forest, Bunyala, and Butula (Fig. 1). Each of these serves as the link between the common tertiary-level center, MTRH, staffed by specialists and sub-specialists, and several primary-level health facilities that feed into it, staffed by clinical officers (mid-level providers) and nurses (Fig. 1).

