Qualitative methods will involve a combination of focus group discussions (FGDs), key informant interviews, and community *mabaraza*, conducted at each level of the health system within each of the six referral network clusters. *Mabaraza* are traditional community assemblies in East African culture and have been used as a novel methodology in community-based participatory research [50, 51]. We will use purposive sampling to recruit patients and clinical staff for the FGDs, and clinic leaders and health system administrators for the key informant interviews. For the mabaraza and FGDs, discussions will be allowed to deviate from the initial guiding discussion topics if additional relevant issues emerge, and participatory techniques will be used to elicit emotional elements and encourage group interaction. Thematic content analysis will be performed, using both deductive (a priori) and inductive (emerging) codes. We will also assess inter-coder reliability, and a kappa-statistic will be calculated.

After the baseline needs and contextual assessment is complete, we will use these data to inform a participatory, iterative design process to fully develop the integrated HIT and peer support STRENGTHS intervention [52–54] A “design team” including a facilitator, research staff, clinical staff, informatics staff, peer navigators, and patients will be formed. The design process will involve three phases: brainstorming, conceptualization, and creation. This design process will use the findings from the baseline needs and contextual assessment alongside input from this diverse group of stakeholders to inform the detailed development of the integrated HIT and peer support intervention protocol. Once the intervention model is developed, we will conduct additional FGDs to assess acceptability [55], as well as a 3-month pilot of the intervention to evaluate feasibility [56].

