### Cluster randomized trial

We will conduct a two-arm cluster randomized trial comparing usual care and referral networks strengthened with an integrated HIT and peer support intervention. The primary outcome measure will be one-year change in SBP and a key secondary outcome will be change in CVD risk score. There will be a total of eight clusters in the trial, four in each arm, with each cluster in a geographically distinct referral network within the overall AMPATH CDM program. First, each referral network cluster will be stratified by size of the health facility at the secondary level. Then cluster randomization will be done within each strata. Cluster randomization will be done using a computerized random number generator in a 1:1 allocation sequence between intervention and control groups. One of the investigators, separate from other research or clinical staff, will generate the allocation sequence and complete randomization. Study staff will then enroll participants in the trial. The trial flow chart is shown in Fig. 4 and the SPIRIT figure is shown in Fig. 5. The SPIRIT checklist is provided in Additional file 1.

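### The power calculation and Table 1 rest on six referral networks, but the trial randomises eight

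*Protocol article*

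**What the plan says.** The protocol article gives two counts for the number of networks.

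- **Eight.** Setting places the study "across eight geographically separate referral networks" and lists eight secondary-level facilities by name. Cluster randomized trial states "There will be a total of eight clusters in the trial, four in each arm", stratified by size of the secondary facility and randomised within strata.
- **Six.** Statistical power opens with "We expect that each of the six referral networks will enroll at least 200 participants". The section on the baseline needs and contextual assessment describes qualitative work "conducted at each level of the health system within each of the six referral network clusters".

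The power section then gives a planned difference of 10 mmHg, error rates of 5% and 20%, ICC from 0.02 to 0.06, SD 15 for Table 1, and up to 15% loss to follow-up. It states neither a total sample size nor the number of clusters behind Table 1. It concludes that power exceeds 80% over a wide range of ICC.

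**The concern.** With so few randomised units, the number of clusters drives the power, both through the variance of the treatment contrast and through the degrees of freedom. If the six in the power section were only a word left over from an older plan, changing it would be enough. If Table 1 was itself computed for six clusters, every power figure in the article belongs to another design, and editing the sentence would leave the table wrong. Planned enrolment is affected as well, because the only recruitment target is a minimum per network.

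**Working it through.** **Inputs**, all from Statistical power unless noted:

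- SD of change 15 mmHg; differences 4 to 14 mmHg; ICC 0.02 to 0.06.
- Type I error 5%. Sidedness is not stated; two-sided is assumed.
- At least 200 enrolled per network. After 15% loss, 200 × 0.85 = 170 analysed.
- k clusters per arm: 3 (six networks at the 1:1 ratio) or 4 (Cluster randomized trial section).

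**Formula**, for equal clusters of size m:

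- SE = √(2 · SD² · [1 + (m − 1) · ICC] / (k · m))
- λ = difference / SE
- power = P(noncentral t with parameter λ exceeds the 97.5% t quantile), df = 2k − 2 if strata are ignored

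**Step 1: reproduce the printed table with six clusters.** Take 10 mmHg, ICC 0.06, k = 3, m = 170. The design effect is 1 + 169 × 0.06 = 11.14. SE = √(450 × 11.14 / 510) = 3.135 and λ = 3.190. With 4 df the critical value is 2.776 and power is 67.0%; Table 1 prints 67. Over all 30 cells the largest deviation is 1.7 points at m = 170 and 0.9 at m = 200. The table therefore cannot show whether the 15% loss was applied. A normal reference in place of t does not reproduce it: at 10 mmHg with m = 170 it gives 99.9/99.1/96.9/93.4/89.1.

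**Step 2: the same cell with eight clusters.** With k = 4, m = 170, SE = √(450 × 11.14 / 680) = 2.715 and λ = 3.683. With 6 df the critical value is 2.447 and power is 86.4%.

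**Step 3: the 10 mmHg row, power in %.**

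| Design | ICC 0.02 | 0.03 | 0.04 | 0.05 | 0.06 |
|---|---|---|---|---|---|
| Table 1 as printed | 96 | 89 | 82 | 74 | 67 |
| 6 clusters, 170 each, 4 df | 96.0 | 89.1 | 81.2 | 73.6 | 67.0 |
| 8 clusters, 170 each, 6 df | 99.8 | 98.4 | 95.4 | 91.2 | 86.4 |
| 8 clusters, 127.5 each, 6 df (total held at 1,200 enrolled) | 99.6 | 97.9 | 94.6 | 90.3 | 85.5 |
| 8 clusters, 170 each, 3 df | 96.1 | 89.8 | 82.5 | 75.5 | 69.2 |

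Over the whole table, eight clusters of 170 with 6 df differ from print by up to 20.0 points (8 mmHg, ICC 0.05: 76.0 against 56), 11 on average, and every cell is higher than printed.

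**Step 4: can any eight-cluster calculation give Table 1?** With SD 15 and 6 df, scanning m from 5 to 400, the closest fit still misses by 8.4 points (m = 33). With 3 df the table is matched within 1.8 points at m = 144, and within 2.5 points at m = 170.

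**Step 5: detectable difference at 80% power**, 170 per cluster, ICC 0.02 to 0.06: 5.7/6.8/7.6/8.4/9.1 mmHg with eight clusters and 6 df, against 7.4/8.7/9.8/10.9/11.8 with six and 4 df.

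**Step 6: implied minimum enrolment.** 6 × 200 = 1,200; 8 × 200 = 1,600.

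**The case against.** The best defence is that Table 1 could come from eight clusters after all. Randomisation is stratified by facility size, and an analysis that fits strata has fewer than 6 df. In the limiting case of four strata of two clusters, df is 3, and the table is then matched within 1.8 points at about 144 per cluster. This stands as a possibility, so it cannot be said that only six clusters reproduce the table. It is the less likely origin: the article states neither matched pairs nor that cluster size, while six networks of 200 stand in the power section itself and fit more closely.

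Three further points are fair. The table is arithmetically sound for six clusters, so the fault is inconsistency and not miscalculation. The second mention of six concerns the qualitative work and is weak evidence of how many networks are randomised. The enrolment figures are derived from a per-network minimum, so they follow from the disputed count and are not a separate contradiction.

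A reader might infer from discrepancies of up to 20 points that the trial is underpowered. The document does not support that. For eight clusters with 6 df the printed figures are too low, not too high.

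**Conclusion.** The point holds. The article randomises eight clusters and reports power that matches six. If eight is the design and strata are not fitted, the error is conservative: at 10 mmHg the claim of power above 80% holds at every listed ICC, whereas the printed row falls below 80% at ICC 0.05 and 0.06 (74 and 67). In the limiting 3-df analysis, power would lie close to the printed values, so the size of the understatement depends on how strata enter the analysis, and the number of strata is not given. In neither case does Table 1 materially overstate the power of eight clusters. Near the ceiling, for example 14 mmHg at ICC 0.02, the difference is about one point.

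These results assume a two-sided 5% test, equal cluster sizes and 15 mmHg as the total SD of change. What needs correcting is the stated basis of the power and the unclear enrolment, not the adequacy of the trial.

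**What to change.** - Make the cluster count in Statistical power, and in the baseline needs and contextual assessment section, agree with Setting and Cluster randomized trial. If only six networks will run, correct those two sections instead.
- State enrolment per cluster and in total. With eight networks and the present minimum this is 1,600 enrolled, and 8 × 170 = 1,360 analysed after 15% loss.
- Recompute Table 1 for the number of clusters actually randomised, with degrees of freedom that match the planned stratified analysis: with eight clusters, 6 if strata are ignored and fewer if they are fitted. Then check the closing sentence on power against the new table.

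The cost is a few sentences and one table. The design does not change and no added enrolment is needed.

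### Table 1 was computed for six clusters, not the eight in the design, so the claim of more than 80% power is an overclaim as printed and should be restated with its ICC and SD limits

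*Protocol article*

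**What the plan says.** All the power inputs are in the Statistical power section.

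- Effect: "We estimate a 10-mmHg reduction in SBP in the intervention arm compared to the usual care arm".
- Error rates: "we set the type I and type II error rates at 5% and 20%, respectively", so the target is 80% power.
- Clustering: "intra-class correlation (ICC) values ranging from 0.02 to 0.06 consistent with prior studies using SBP as the outcome".
- Variability: "assuming a standard deviation (SD) for change in SBP of 15 from the literature, with SD ranges from 10 to 20".
- Networks: six, each enrolling at least 200, with up to 15% lost to follow-up.
- Table: "Table 1 presents expected power assuming a standard deviation of 15 for the comparison". Its 10-mmHg row is 96, 89, 82, 74 and 67% for ICC 0.02, 0.03, 0.04, 0.05 and 0.06.
- Conclusion: "Over a wide range of plausible ICC, with standard deviation fixed at 15, we will be able to detect a mean difference" in line with the literature and the preliminary data, "with power greater than 80" per cent.

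The number of clusters differs elsewhere. The Setting section names eight secondary-level facilities, each the centre of a referral network. The Cluster randomized trial section fixes eight clusters, four in each arm, with 1:1 allocation.

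**The concern.** The concluding sentence gives no figure for the difference and no upper limit for the ICC. The only effect the section names as expected is 10 mmHg and the only ICC range it names is 0.02 to 0.06, so a reader will put those two together. Table 1 does not support that combination at ICC 0.05 (74%) or 0.06 (67%). Every column reaches 80% only from 12 mmHg, which is more than the plan expects.

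The table also describes a trial with fewer clusters than the one being run. In a design this small, moving from three to four clusters per arm changes power a great deal, because it raises the degrees of freedom from 4 to 6 as well as reducing the standard error. The published figures are therefore not the power of the actual design, and anyone interpreting a null result would be working from the wrong numbers.

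**Working it through.** **Method.** With k clusters per arm, m analysed per cluster, standard deviation SD and difference d:

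- design effect DE = 1 + (m − 1) × ICC
- SE = SD × √(2 × DE / (k × m))
- power = probability that a noncentral t with 2(k − 1) degrees of freedom and noncentrality d / SE exceeds the two-sided 5% critical value.

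The article does not say whether the 5% is one- or two-sided; two-sided reproduces the table.

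**Step 1: reproduce Table 1.** Take k = 3 (six networks at 1:1), m = 200, SD = 15, d = 10. The critical value on 4 df is 2.776.

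- ICC 0.05: DE = 1 + 199 × 0.05 = 10.95; SE = 15 × √(21.90 / 600) = 2.866; noncentrality 3.489; power 74.2% (printed 74).
- ICC 0.06: DE = 12.94; SE = 15 × √(25.88 / 600) = 3.115; noncentrality 3.210; power 67.5% (printed 67).

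All 30 cells of Table 1 agree within 0.93 percentage points. With m = 170 (200 less 15%), all agree within 1.7 points. With k = 4 and m = 170 the 10-mmHg row would be 99.8, 98.4, 95.4, 91.2 and 86.4%, which does not match. Table 1 is therefore correct arithmetic for six clusters.

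**Step 2: where the six-cluster table reaches 80%.** At 10 mmHg and SD 15, power is 80% or more only up to an ICC of about 0.042. The difference detectable with 80% power is 10.8 to 10.9 mmHg at ICC 0.05 and 11.7 to 11.8 mmHg at ICC 0.06.

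**Step 3: recompute for eight clusters.** Now k = 4, with 6 df and critical value 2.447. The article gives 200 per network only for six networks, so enrolment per cluster is an assumption. Two cases bracket it:

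- (a) 200 in each of eight clusters, 1600 in all; 200 × 0.85 = 170 analysed per cluster
- (b) total unchanged at 6 × 200 = 1200; 150 per cluster, 150 × 0.85 = 127.5 analysed.

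Worked cells at 10 mmHg:

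- (a) SD 15, ICC 0.06: DE = 1 + 169 × 0.06 = 11.14; SE = 15 × √(22.28 / 680) = 2.715; noncentrality 3.683; power 86.4%.
- (b) SD 15, ICC 0.06: DE = 1 + 126.5 × 0.06 = 8.59; SE = 15 × √(17.18 / 510) = 2.753; noncentrality 3.632; power 85.5%.
- (a) SD 20, ICC 0.04: DE = 7.76; SE = 20 × √(15.52 / 680) = 3.021; noncentrality 3.310; power 78.7%.

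Power (%) at 10 mmHg:

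| Design | SD | ICC 0.02 | 0.03 | 0.04 | 0.05 | 0.06 |
|---|---|---|---|---|---|---|
| Table 1 as printed (six clusters) | 15 | 96 | 89 | 82 | 74 | 67 |
| Eight clusters, (a) | 15 | 99.8 | 98.4 | 95.4 | 91.2 | 86.4 |
| Eight clusters, (b) | 15 | 99.6 | 97.9 | 94.6 | 90.3 | 85.5 |
| Eight clusters, (a) | 20 | 95.3 | 87.4 | 78.7 | 70.6 | 63.7 |
| Eight clusters, (b) | 20 | 94.0 | 85.7 | 77.1 | 69.3 | 62.5 |

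At SD 10, power with eight clusters is above 99% throughout in both cases.

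**The case against.** A reader might infer that Table 1 flatly contradicts the concluding sentence. The documents do not go that far. The sentence speaks of a wide ICC range, not the whole of it. It ties the detectable difference to literature and preliminary data whose values the article does not give, and the 10-mmHg estimate is cited to a different source. Table 1 supports the sentence at 10 mmHg for ICC 0.02 to 0.04, and at every ICC from 12 mmHg. The 74 and 67 are printed in the table for anyone to see. All of this stands, and it is why the fault is an overclaim and not a contradiction.

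A reader might also infer that the trial is underpowered for 10 mmHg at SD 15. That does not follow either. The shortfall belongs to the six-cluster calculation; with the eight clusters of the design it disappears.

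On the SD, the section says openly that both table and conclusion hold it at 15, and showing only the base case is ordinary condensation in an article. So the untabulated SDs are a secondary point, and the plan did not conceal its condition. The point keeps some weight because the section itself announces a range ("with SD ranges from 10 to 20"), and the conclusion changes within that range even after the cluster number is corrected.

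**Conclusion.** The point holds as an overclaim with an identifiable cause. As printed, the conclusion is unsupported at two of the plan's five ICC values for its own expected effect, by 6 points at ICC 0.05 and 13 points at ICC 0.06. The cause is a six-cluster input that does not match the eight-cluster design.

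For eight clusters the corrected position is more favourable at SD 15: at least 85% at every stated ICC, with a margin that extends to an ICC of about 0.07. It is less favourable than the text suggests at SD 20, where 80% power for 10 mmHg is reached at ICC 0.02 and 0.03 but not at 0.04 or above. Neither statement depends on which enrolment figure is used.

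The recomputed figures assume equal cluster sizes, an ICC that applies to the change in SBP, a two-sided 5% test, no precision gained from baseline adjustment, and no degrees of freedom lost to stratification. Unequal clusters or lost degrees of freedom would lower them; a useful baseline adjustment would raise them.

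**What to change.** 1. Change the number of networks in the Statistical power section from six to eight, and state the enrolment per cluster and the number analysed after 15% loss.
2. Recompute Table 1 for four clusters per arm, naming the test, its sidedness and its degrees of freedom.
3. Add rows for SD 10 and SD 20, at least for the 10-mmHg effect.
4. Replace the concluding sentence with one that carries its own limits. On the assumptions above it could read: for a 10-mmHg difference with eight clusters, power is at least 85% for ICC 0.02 to 0.06 at SD 15; at SD 20 it exceeds 80% up to ICC 0.03 and falls to about 63% at ICC 0.06. The exact figures should follow from the enrolment stated under item 1.

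The cost is text and a few table rows. The design, sample and analysis do not change. The figures at SD 15 improve, and a less favourable figure is shown at SD 20.

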### Analytical approach

We will use an analysis of covariance model with cluster effects to estimate and draw inference about treatment effects for both primary and key secondary outcomes. The model specification is:
$$ {\mathrm{y}}_{\mathrm{ij}}=\upalpha +{\upgamma}_{\mathrm{j}}+{\upbeta}_1{\mathrm{x}}_{\mathrm{ij}}+\uptheta {\mathrm{b}}_{\mathrm{ij}}+{\mathrm{e}}_{\mathrm{ij}} $$

where y_ij_ is SBP at the end of follow-up for the ith individual in the jth cluster, b_ij_ is baseline SBP, and the indicators x_ij_ represent intervention group membership, with usual care as the reference. Hence, β coefficient represents the difference in mean change in SBP between usual care and the intervention. The intercept is α and γ_j_ is the effect of the jth cluster. Cluster effects γ_j_ will initially be modeled as fixed effects, but we will use a mixed model structure and assign a normal distribution if the data support this assumption. We will compare key independent variables across the trial arms to ensure balance of the randomization process and adjust the model to estimate treatment effects as needed. For modeling QRISK2, we will use the transformation log(−log (QRISK2)) because the risk score ranges from 0% to 100% [73]. We will test the further hypotheses that changes in referral network characteristics and referral process metrics can mediate the effect of the intervention on CVD outcomes, and that baseline referral network characteristics can moderate the effect of the intervention on outcomes, by conducting a mediation and moderation analysis, respectively [74, 75]. Further details of the data management procedures and statistical methods, including approach to missing data, mediation and moderation analysis, and secondary outcomes, are available upon request from the authors.

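### The primary model starts with fixed cluster effects, under which the treatment effect is not identifiable; the estimable mixed model in the same sentence is only conditional

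*Protocol article*

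**What the plan says.** Under Cluster randomized trial, the protocol article randomises whole referral networks: "There will be a total of eight clusters in the trial, four in each arm". Allocation is 1:1 between arms, within strata of secondary-facility size.

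Under Analytical approach it states: "We will use an analysis of covariance model with cluster effects to estimate and draw inference about treatment effects", and it applies this to the primary and key secondary outcomes. The printed equation is y_ij = α + γ_j + β₁x_ij + θb_ij + e_ij, where γ_j is the effect of cluster j and b_ij is baseline SBP. The x_ij "represent intervention group membership, with usual care as the reference". The β coefficient is described as the between-arm difference in mean change in SBP. On γ_j, the rule reads: "initially be modeled as fixed effects, but we will use a mixed model structure and assign a normal distribution if the data support this assumption". No constraint on γ_j is given, and no cluster-level alternative.

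Under Statistical power the number of networks is six: "We expect that each of the six referral networks will enroll at least 200 participants".

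**The concern.** Everyone in a network is in the same arm, so x_ij does not vary within a cluster. Once each cluster has its own free intercept, nothing remains from which to estimate an arm difference. The meaning the article gives to β therefore does not hold under the specification named as the starting point.

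The second half of the sentence does lead to a model that works, but only on a condition. Read naturally, the condition is that the data support a normal distribution for the cluster effects. Six or eight values say very little about that, so the choice of primary model rests on a check with almost no information. If the check is judged to fail, the remaining model does not answer the trial's question. The primary SBP comparison and the QRISK2 comparison both depend on this, and the cost-effectiveness analysis takes its effectiveness measures from them.

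**Working it through.** **Inputs.** From Cluster randomized trial: eight clusters, four per arm. From Statistical power: six networks of at least 200, SD of change in SBP 15, ICC 0.02 to 0.06, loss to follow-up up to 15%, type I error 5% (taken as two-sided; the article does not say). Analysed per cluster: 200 × 0.85 = 170.

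**1. What the power table assumes.** Take SE = SD·√(2(1 + (m−1)·ICC)/(k·m)), with k clusters per arm and a two-sided 5% noncentral t test on 2k−2 df. For a 10 mmHg difference and ICC 0.02, 0.03, 0.04, 0.05, 0.06:

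| Source | Power (%) |
|---|---|
| Table 1 | 96 / 89 / 82 / 74 / 67 |
| k = 3, m = 170, 4 df | 96.0 / 89.1 / 81.2 / 73.6 / 67.0 |
| k = 4, m = 170, 6 df | 99.8 / 98.4 / 95.4 / 91.2 / 86.4 |

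Table 1 reproduces with three clusters per arm on 4 df. Over all 30 cells the largest difference is 1.7 points at m = 170 and 0.9 at m = 200. The trial was therefore powered on between-cluster variance, which fixed cluster effects remove from the error term.

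**2. Identifiability.** The columns are intercept, (number of clusters − 1) cluster indicators, x and baseline SBP.

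- Eight clusters: 1 + 7 + 1 + 1 = 10 columns, rank 9. Without x the rank is still 9.
- Six clusters: 1 + 5 + 1 + 1 = 8 columns, rank 7. Without x the rank is still 7.

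So x adds nothing to the column space and β is not identified. This needs no assumed figure and holds for either cluster count.

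**3. What software might return.** It may drop x, which gives no estimate. Or it may drop a further cluster indicator, and β then becomes the adjusted difference between one intervention network and one control network. Two data sets were simulated with a true effect of −10, ICC 0.04 and 8 × 170 participants, using four choices of omitted indicators. In the first, the coefficient ran from −18.6 to −10.7; in the second, from −14.1 to +0.9. The residual sum of squares was identical within each data set. The mixed model gave a single answer for each: −13.4 (SE 1.8) and −9.1 (SE 2.8).

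**4. Size of the error if such a contrast were reported.** Let σ_b² = ICC × 225 and σ_w² = (1 − ICC) × 225.

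- Model SE = √(2σ_w²/170). ICC 0.02: √(2 × 220.5/170) = 1.61. ICC 0.06: √(2 × 211.5/170) = 1.58.
- True SD = √(2σ_b² + 2σ_w²/170). ICC 0.02: √(9 + 2.59) = 3.41. ICC 0.06: √(27 + 2.49) = 5.43.
- Type I error = 2[1 − Φ(1.96 × model SE/true SD)]. Results for ICC 0.02 to 0.06: 0.354, 0.433, 0.491, 0.534, 0.569.

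The SD cancels from the ratio, which is √((1 + (m−1)·ICC)/(1 − ICC)), so only ICC and m matter for the error rate. If the 6 × 200 = 1,200 participants are spread over eight clusters, m = 1,200 × 0.85/8 = 127.5 and the range is 0.302 to 0.517.

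**5. The most charitable constraint.** Suppose γ_j is forced to sum to zero within each arm, which the article does not state. Then β is estimable as a difference of arm averages over four clusters. The model SE is about 0.8 against a true SE of 1.7 to 2.7 (m = 170). The ratio is the same as in step 4, so the error rate is again about 35% to 57%.

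**The case against.** The strongest reply is that the sentence does not stop at fixed effects: it goes on to a mixed model, under which β is estimable. That stands. A reader might infer from the equation that the trial has no estimable primary analysis at all, and the document does not support this. The defect lies in the starting form and in the condition attached to the alternative.

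A reader might also take 35% to 57% as the error rate of the plan as written. It is not. It needs the mixed model to be set aside, and then either software that drops an indicator and an analyst who reports the result, or an unstated within-arm constraint. If x is dropped instead, there is no test. The figure also combines 170 per cluster, from a section that counts six networks, with the eight clusters given elsewhere. The mmHg figures further use the SD of change as the residual SD of the covariance model.

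A third inference would be that the mixed model will be tested against a normal reference and so be too liberal with few clusters. The article names no reference distribution or degrees of freedom, which is ordinary analysis-plan detail, so this is no stated error.

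It could finally be said that the whole matter belongs in the analysis plan. That does not stand: the article prints the equation, names the starting form and gives the switching rule. The question is about a rule it states, not a detail it leaves out.

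**Conclusion.** The point holds in this form. Under the fixed-effect starting specification the treatment effect is not identifiable, for six or eight clusters, as a matter of algebra. The model that can estimate it is made conditional on a distributional judgement that so few clusters can hardly support, and the fallback if the judgement fails is unusable. This affects the primary and key secondary analyses and should be corrected before analysis.

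The numerical consequence is illustrative only: type I error of about 35% to 57% at 170 analysed per cluster, or about 30% to 52% at about 127, over ICC 0.02 to 0.06 and only under the reporting behaviour described. The finding does not depend on those figures.

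**What to change.** Delete the fixed-effect step and the condition on the data. State as the unconditional primary model an analysis of covariance with a random intercept per network, or a cluster-level analysis of baseline-adjusted cluster means, and use the same structure for transformed QRISK2. The two approaches coincide only when cluster sizes are balanced, so name one as primary.

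Base inference on cluster-level degrees of freedom with a small-sample correction such as Kenward-Roger or Satterthwaite. With eight clusters this is at most 6 df, and fewer if the facility-size strata used in randomisation enter the model; say whether they do. Do not justify 6 df by reference to Table 1, which corresponds to three clusters per arm and 4 df.

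The cost is a change of wording and no new data. The confidence interval will be wider than one that ignores between-cluster variation, which is the correct width for this design.
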